### 2.2. Study Power

A formal sample size calculation is not required since this is a pilot feasibility study. However, by hypothesizing a 2-point change and moderate effect size (γ = 0.60) on the QOC questionnaire filled in by family carers at T2, with a power of 0.85, 2-sided α = 0.05, and 20% of family carers lost at T2, we aim to recruit at least 40 family carers. The 2-point change on the QOC questionnaire was based on the hypothesis that the intervention would improve at least two QOC items by 1 point [16]. 

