### 2.3. Data Analysis

#### 2.3.1. Quantitative Data

Descriptive statistics will be employed. Categorical variables will be summarized as numbers and percentages, while continuous variables will be summarized as mean and standard deviation (SD), or median and interquartile range (IQR). Categorical variables will be compared using the χ^2^. The Shapiro–Wilk test will be adopted to test the normality assumption of continuous variables. Depending on the data distribution, the paired t-test or the Wilcoxon signed-rank test will be carried out; correlations will be computed using Pearson’s or Spearman’s coefficients. As an additional analysis of the temporal change in the primary outcome (i.e., the quality of communication as perceived by family carers), a linear regression analysis using time as a covariate will be used to test for a trend in the quality of communication. As the analysis will be performed at the family carer level, the Huber–White estimator will be used to adjust for the correlation between the multiple observations contributed by the same NH. A significant coefficient of the time variable will indicate that the primary outcome changes with respect to time. The goodness of fit will be evaluated by R^2^.

Change in the secondary outcome measures will be calculated, as well as the following feasibility outcomes: recruitment rate of HCPs engaged in the training program (and reasons for non-enrolment); retention rate (proportion of HCPs completing the training program; proportions of family carers and HCPs completing follow-ups); missing data (proportion fully completed for each scale at each time point). In the case of missing values, multiple imputation will be performed. A p value less than 0.05 will be considered statistically significant. All analyses will be performed using SPSS v. 27. 

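### The additional regression of family-carer QOC on time has no carer term, so its slope can mix within-carer change with change in who remains unless imputation covers missed visits

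*Protocol article*

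**What the plan says.** Protocol article, section 2.3.1, makes a paired comparison the pre-post test: depending on the distribution, "the paired t-test or the Wilcoxon signed-rank test will be carried out". It then adds a second analysis, introduced by "As an additional analysis of the temporal change in the primary outcome", in which "a linear regression analysis using time as a covariate will be used to test for a trend in the quality of communication". Time is the only covariate named. A Huber–White variance handles correlation among observations from the same nursing home, and a significant time coefficient is read as change in the primary outcome. On fit, the section says: "The goodness of fit will be evaluated by" R². A later sentence provides for multiple imputation of missing values. It does not say whether that means incomplete questionnaires, missed visits or both, or which variables enter the imputation model.

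The section on quality of communication has each carer rate the QOC at T0, T1 and T2. Section 2.2 plans for "20% of family carers lost at T2" and states the target "by hypothesizing a 2-point change and moderate effect size (γ = 0.60) on the QOC questionnaire filled in by family carers at T2".

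**The concern.** The regression uses up to three ratings per carer but does not identify the carer. With complete data this leaves the slope unchanged, because every carer contributes the same three times. With losses it matters: the T2 mean then comes from those who stayed, while the T0 mean comes from everyone. If carers who gave low ratings at T0 leave more often, the fitted trend rises although nobody's rating has changed. A cluster-robust variance cannot correct this, because it alters the standard error and not the coefficient.

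R² from this model has all between-carer variation in its denominator. It therefore falls as carers differ more from one another, whether or not each of them follows the trend.

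Box 1 says the pilot is to estimate the primary outcome and to inform the sample size of later studies. A slope partly made by drop-out would be a poor input for that.

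**Working it through.** **1. The plan's own figure.** Inputs from section 2.2: effect size 0.60, "with a power of 0.85, 2-sided α = 0.05, and 20% of family carers lost at T2", and "we aim to recruit at least 40 family carers".

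- Normal approximation: ((1.960 + 1.036)/0.60)² = 24.9, so 25; 25/0.8 gives 32.
- Paired t-test: 27; 27/0.8 gives 34.
- Wilcoxon signed-rank at its minimum efficiency of 0.864: 27/0.864 = 31.25, so 32; 32/0.8 = 40.

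The stated 40 is reproduced by the last route. The article does not name its formula, but the match is consistent with reading 0.60 as a paired effect. On that reading the SD of change is 2/0.60 = 3.33.

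**2. Score SD.** The article gives neither a score SD nor a within-carer correlation ρ. With SD of change 3.33, score SD = 3.33/√(2(1−ρ)): 3.33, 4.30, 5.27 and 7.45 at ρ = 0.5, 0.7, 0.8 and 0.9. These correlations are assumptions.

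**3. Slope when loss depends on the T0 rating, no true change, no imputation.** Assume 40 carers, visits at 0, 1 and 6 months, and 20% lost at T2, with the log-odds of loss rising by β = 0.5 to 0.8 per SD of lower T0 rating.

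- The T0 mean of those who stay lies k SDs above that of all carers, where k = β·E[p(1−p)]/0.8 and p is the loss probability. For β = 0.5, E[p(1−p)] ≈ 0.154 and k ≈ 0.096. For β = 0.8, E[p(1−p)] ≈ 0.145 and k ≈ 0.145.
- The observed T2 mean is then too high by ρ × SD × k.
- With 40, 40 and 32 ratings at months 0, 1 and 6, mean time is 232/112 = 2.071 and the sum of squares of time is about 711. The fitted T0–T2 change is 6 × 32 × (6 − 2.071)/711 ≈ 1.06 times that shift.
- Example, ρ = 0.7 and β = 0.8: 0.7 × 4.30 × 0.145 × 1.06 = 0.46 points.

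| ρ | Spurious rise, closed form | Spurious rise, simulated (about 20% loss) | Random carer intercept |
|---|---|---|---|
| 0.5 | 0.17–0.26 | 0.17–0.27 | about 0 |
| 0.7 | 0.31–0.46 | 0.32–0.53 | about 0 |
| 0.8 | 0.43–0.65 | 0.45–0.69 | about 0 |
| 0.9 | 0.68–1.03 | 0.71–1.12 | about 0 |

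The two routes agree to within about 0.1. Against the 2-point target, 0.17 to 1.12 is 8% to 56%.

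**4. Loss at random.** The pooled slope is then unbiased, but the random intercept lowers its empirical standard error: 0.61 to 0.54 at ρ = 0.7, and 0.78 to 0.56 at ρ = 0.9.

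**5. With imputation.** A separate simulation used a true rise of 2 points and a stronger link between low T0 rating and loss. At ρ = 0.5, 0.8 and 0.9 the pooled slope on observed data gave 2.44, 3.09 and 3.75. The same regression after imputing T2 from the carer's own T0 and T1 gave 2.00, 2.00 and 1.98.

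**6. R² under the planned effect.** The means at 0, 1 and 6 months are 0, 0.33 and 2, with variance 0.765. Pooled R² = 0.765/(0.765 + SD²).

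- ρ = 0 (SD² = 5.56): 0.121
- ρ = 0.5 (SD² = 11.1): 0.064
- ρ = 0.9 (SD² = 55.6): 0.014
- ρ = 0.95 (SD² = 111): 0.007

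Within carers the residual variance is 5.56 × 2/3 = 3.70 whatever ρ is, so the within-carer R² is 0.765/(0.765 + 3.70) = 0.17 throughout. The trend and the noise around it are the same in every row. Only the spread between carers moves the pooled R².

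**The case against.** The best defence is that the article already plans multiple imputation. If that fills missed T2 scores from each carer's T0 and T1, every carer contributes all three times and the bias goes (step 5). This stands in full for that reading. But the sentence leaves its scope open, and it follows a definition of missing data as the share of each scale fully completed, so it may concern incomplete questionnaires only. Detail of that kind may sit in a fuller plan. The point is therefore conditional on it.

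Second, a reader might infer that the trial's main result could be made by drop-out. The article does not support this. The regression is labelled additional, and the paired test compares each carer with themselves. That test has its own dependence on who completes T2, but that is a separate matter.

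Third, a reader might assume a score SD of 10 or 20 and find a spurious rise that rivals or exceeds the target. At ρ = 0.7 those SDs imply SDs of change of 7.7 and 15.5, hence effect sizes of 0.26 and 0.13, which conflict with the planned 0.60.

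Fourth, it is tempting to say that R² is always near zero and would be taken as lack of fit. It is low rather than always near zero, and the stated criterion is the significance of the time coefficient.

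Finally, some residents are enrolled with death expected within weeks or months. For carers lost that way, what a T2 rating would mean is open under either imputation or a mixed model. The article does not give their share, so no size can be put on this.

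**Conclusion.** The point holds in a limited form. As written, the additional regression does not separate within-carer change from change in who remains, unless the multiple imputation covers missed visits and uses each carer's earlier scores. Without that, and with about 20% loss related to the T0 rating, the spurious rise is about 0.2 to 1.1 points against a target of 2. This rests on the paired reading of the 0.60 effect size, an assumed correlation of 0.5 to 0.9 and an assumed loss log-odds of 0.5 to 0.8 per SD. If loss is unrelated to the rating there is no bias, only a larger standard error than needed. R² of about 0.01 to 0.12 measures how much carers differ, not whether the trend fits, but nothing is decided on it. The consequence is confined to a secondary analysis of a pilot.

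**What to change.** In section 2.3.1, replace the pooled regression with a linear mixed model of QOC on time with a random intercept per carer, using all observed visits. Prefer this to carer fixed effects: when loss depends on the T0 rating, fixed effects are biased slightly downward (−0.04 to −0.14 points in the settings of step 3). State whether multiple imputation applies to missed visits and, if so, that each carer's earlier scores enter the imputation model. Drop R² as the fit criterion and report the estimated T0–T2 change with its 95% confidence interval.

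The cost is analysis wording only. No extra data are needed.

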**(ii)** 
**Pilot pre-post study**

Four NHs will be purposefully involved in the pilot feasibility pre-post study and sampled for geographical area and size to ensure the greatest variation of data. All NHs will be located in the northwest of Italy and will participate on a voluntary basis. Participation will be promoted through a local nursing home association network. 

There will be a baseline assessment (T0), the beginning of the training program within 1 month of the baseline assessment, and a follow-up assessment within 4 weeks of the initiation of the training program (T1) and 6 months (T2) thereafter. The baseline and follow-up assessments will be performed via anonymized records filled in by paper and pencil. A member of the research team will input the collected data into a password-protected database accessible only to the team members.

Participants (NH staff, family carers) will be free to withdraw from the study at any time, without giving reasons and without consequence. Information about drop-out reasons will be collected. 

The objectives of the pilot feasibility pre-post study are reported in Box 1. The study procedures are shown in Figure 2.

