##### Eligibility and Screening

HCPs (a) of any profile, (b) with at least 6 months experience in the facility, (c) responsible for serious illness conversations with family carers, and (d) willing to participate in the study, will be eligible. Administrative staff will be excluded as their role does not involve clinical conversations with family carers. 

The main family contact for all institutionalized residents will be included if they are: ≥18 years, capable of communicating in Italian, and gave their written consent, regardless of the point of care of their relative (i.e., transition phase to the nursing home [38], deterioration-in-condition phase [39], or end-of-life phase with death expected within the next few weeks or within a few months [40]).

The number and profile of HCPs to be trained will be agreed upon with each participating facility according to their internal processes of communication with family carers. Anyway, it will be recommended to train at least three, four, and five HCPs in facilities with less than 50 beds, 50 to 100 beds, and more than 100 beds, respectively. No minimum nor maximum number of family carers per NH will be prespecified.

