##### Outcome Measures 

A range of measures will be collected to capture the effect of the *Teach-to-communicate* training program at multiple levels:

Family carers: quality of communication, burden, quality of care, satisfaction with the care received;

HCPs: quality of communication, confidence in and obstacles to serious illness conversations;

Residents: completion of any ACP documents.

The primary outcome is the quality of communication perceived by family carers at T2. Outcomes with their assessment tools are reported in Table 2. 

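### The additional regression on the primary outcome clusters its Huber–White variance on only four nursing homes; without a small-sample reference, its p<0.05 rule is too liberal

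*Protocol article*

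**What the plan says.** The Protocol article, under Outcome Measures, states: "The primary outcome is the quality of communication perceived by family carers at T2". Section 2.3.1 gives two routes for testing change.

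- **Pre-post comparison:** "Depending on the data distribution, the paired t-test or the Wilcoxon signed-rank test will be carried out". Nursing home does not enter this test.
- **Additional analysis of the primary outcome:** "a linear regression analysis using time as a covariate will be used to test for a trend in the quality of communication". For this model "the Huber–White estimator will be used to adjust for the correlation between the multiple observations contributed by the same NH". The decision rule is: "A significant coefficient of the time variable will indicate that the primary outcome changes with respect to time". The threshold is: "A p value less than 0.05 will be considered statistically significant".

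On the number and size of the clusters, the section on the pilot pre-post study says "Four NHs will be purposefully involved in the pilot feasibility pre-post study" and adds that homes are sampled to differ in area and size. Eligibility and Screening says "No minimum nor maximum number of family carers per NH will be prespecified". Unequal clusters are therefore likely.

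Section 2.2 gives the planning figures: effect size 0.60, power 0.85, two-sided 5%, 20% loss and at least 40 carers.

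**The concern.** A cluster-robust sandwich variance is justified by a large number of clusters, not of carers. With four clusters the variance is estimated from four home-level contributions. The test statistic then behaves roughly like a t on 3 df, whose 5% critical value is 3.18, not 1.96. If the usual reference is used, an apparent trend can reach p<0.05 far more often than one time in twenty when nothing has changed. The plan turns that p-value into a statement about its primary outcome, and intervals of the same kind would be too narrow for planning the next study.

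A second, conditional matter is the paired test. The plan allows for correlation within a home in the regression but not in this test, so the reach of its p-value needs to be stated.

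**Working it through.** **Inputs.** From the documents: G = 4 homes, three visits (T0, T1, T2), alpha 0.05, effect size 0.60, 40 carers recruited, 20% loss, hence 40 × 0.8 = 32 completers. Assumed, because the documents do not give them: the split of carers over homes (8 each, or 3/5/8/16; also 10 each, or 22/8/6/4, for 40 carers) and the intracluster correlation (ICC) of change, taken from 0 to 0.20.

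**1. The plan's own figure.** A paired t-test with effect size 0.60, power 0.85 and two-sided 5% needs 27 completers. Dividing by the minimum relative efficiency of the Wilcoxon test, 27/0.864 = 31.25, so 32; then 32/0.8 = 40. The stated 40 is reproduced. It contains no term for nursing home.

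**2. Huber–White with four equal homes.** With equal homes and complete visits, the fitted slope is the mean of the four home slopes, and the sandwich uses only their spread.

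- Uncorrected: the SE is √((G−1)/G) = √(3/4) = 0.866 of what it should be. The false-positive rate against 1.96 is P(|t₃| > 1.96 × 0.866 = 1.70) = 0.188.
- With the G/(G−1) factor: the SE is unbiased, but P(|t₃| > 1.96) = 0.145. With t on 94 df (32 × 3 − 2) it is 0.141.
- Width of the 95% interval relative to the t₃ interval: 1.96 × 0.866/3.18 = 0.53 uncorrected; 1.96/3.18 = 0.62 corrected.

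The ICC does not enter these results, because the spread of the home slopes already contains it.

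**3. Simulated type I error of the time coefficient** (no true mean change, 8,000 runs per setting, ICC of change 0 to 0.20):

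| Homes | Uncorrected, 1.96 | G/(G−1), normal or t(94) | G/(G−1), t(3) |
|---|---|---|---|
| 8/8/8/8 | 0.18–0.20 | 0.14–0.15 | about 0.05 |
| 3/5/8/16 | 0.22–0.27 | 0.16–0.21 | 0.06–0.09 |

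For 22/8/6/4, the rate without the t(3) reference was 18–27%, and with it 7–9%.

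**4. Paired t-test.** Differencing removes stable differences in level between homes. What remains is variation in change. For a population of homes, with 8 carers per home, the design effect is 1 + 7 × ICC:

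| ICC of change | Design effect | SE as share of true SE | Type I, 8/8/8/8 | Type I, 3/5/8/16 |
|---|---|---|---|---|
| 0 | 1.00 | 1.00 | 0.05 | 0.05 |
| 0.05 | 1.35 | 0.86 | 0.09 | 0.11 |
| 0.10 | 1.70 | 0.77 | 0.14 | 0.16 |

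With 40 carers and ICC 0.10 the rate is 15% for equal homes and 21% for 22/8/6/4. If the null concerns only the carers of these four homes, the same test rejects 4.1–4.4%, so it is slightly conservative.

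**5. Price of the 3-df reference.** For a home-level test of the T2–T0 change with 32 completers in equal homes, the noncentrality is 0.60 × √(32/design effect) = 3.39, 2.92 and 2.60 at ICC 0, 0.05 and 0.10. Against 3.18 on 3 df the power is 0.63, 0.51 and 0.43, compared with the planned 0.85.

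**The case against.** **Additional analysis, pilot.** The regression is labelled additional, and most of the objectives in Box 1 concern feasibility or estimation. This stands and lowers the severity. It does not remove the point: the plan attaches an explicit decision rule to that coefficient, and Box 1 wants the results to inform later sample sizes.

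**Reference df belong in an analysis plan.** A separate plan may give them, so this stands in part. But the article fixes the estimator, the cluster unit, the number of clusters and the threshold, and that combination misleads unless the correction accompanies it.

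**Target of inference.** The rates in step 3 treat homes as a sample. If change varies between homes and the question is confined to these four, the excess is smaller. At zero ICC the two readings coincide and the inflation is still there.

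**Stronger readings that a reader might infer:**

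- *Both analyses give standard errors that are too small.* Not supported. The paired test's SE is too small only if change varies between homes and inference goes beyond them; no ICC is given. With equal homes and the G/(G−1) factor, the Huber–White SE is also unbiased, and it is the reference distribution that fails.
- *A model with fixed home and home-by-time effects cures the paired test.* It does not for wider inference. At ICC 0.10 it rejects 17% with 10 carers per home and 13% with 22/8/6/4. It also weights homes equally; with 3/5/8/16 that cuts the effective sample from 32 to 22 (16/(1/3 + 1/5 + 1/8 + 1/16) = 22.2).
- *The Shapiro–Wilk step inflates error.* A rate of 11%, against 6% for the t-test, arises with a chosen skewed distribution of differences. With symmetric differences the two-stage rule gives 4.7–5.3%. What remains is that the data choose the hypothesis, a secondary point.
- *Linear time is invalid.* A trend test is valid under no change, and unequal spacing does no harm if time is entered in actual units.

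**Conclusion.** The point holds for the clustered regression. With four homes and a normal or large-df reference, a nominal 5% test has a false-positive rate of about 14–19% with equal homes and about 16–27% with the unequal splits tried. The equal-home figures follow from the t₃ distribution and need no assumed ICC; the unequal-home figures depend on the assumed split and, to a lesser degree, on the ICC.

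For the paired test only a limit on interpretation follows. It is valid for carers in the four purposively chosen homes. Its type I error for other homes would be about 9–21% if the ICC of change were 0.05–0.10, which is an assumption. The sample size of 40 is not wrong on its own terms.

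The regression rule should be corrected before analysis. It is not a critical fault, because it concerns an additional analysis in a pilot.

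**What to change.** In section 2.3.1:

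1. State that the Huber–White variance clustered on nursing home uses the G/(G−1) correction and that the time coefficient is referred to a t distribution on 3 df, for both the p-value and the 95% interval. Note that with unequal homes the error rate remains slightly above nominal (6–9%).
2. Report the T2–T0 change in the primary outcome for each home with a 95% interval.
3. State that the paired t or Wilcoxon result applies to the four participating homes only.

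No new data are needed, and the change is a few sentences. The cost is statistical: the corrected interval is 3.18/1.96 = 1.62 times as wide as one built with 1.96 on the same SE. A home-level test has power of about 0.43–0.63 at the planned effect, not 0.85, and a home with very few carers will have a very wide interval. A fixed home-by-time model is not required.

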#### 2.3.2. Qualitative Data

Interviews will be audio-recorded and transcribed verbatim. Data analysis will be conducted by three researchers who have experience in qualitative research. Transcripts will be analyzed using inductive content analysis [48] with the aid of ATLAS.ti 8.4.26.0 software. A coding sheet will be developed following an iterative process of discussion among the research team. Transcripts will be read carefully several times, and a summary of excerpts will be generated and coded. All transcripts will be reread as new codes develop. Similar codes will be gathered into categories, and similar categories into themes. The themes will be illustrated by the interviewees’ quotations, which will be identified by an alphanumeric code.

### 2.4. Data Management

All data will be stored on a password-protected computer and a central hard disk from the research team. The data of the participants will be pseudonymized, and only the principal investigator will be able to link raw data to personal data. Data will be stored for a minimum of 5 years after the appearance of publications based on this database. After this period, the data can be destroyed.

### 2.5. Public Involvement

A representative of the Piedmont Alzheimer’s Association and a representative of the Light For Life Onlus are part of the Steering Committee of the project and will be part of the interdisciplinary panel responsible for co-designing the booklet. 

